#### Controlling the SAA content of the intervention

To regulate SAA content of the diets, capsules with (SAA_high_) or without (SAA_low_) methionine and cysteine will be provided in a double-blind manner. The SAA_low_ group will receive capsules with no SAA (3000 mg/days maltodextrin) (capsules: Capsuline, Florida, USA; maltodextrin: (Star Nutrition, Sweden), whereas the SAA_high_ group will receive capsules with methionine (1125 mg/days) and cystine (2500 mg/days) (Jo Mar Laboratories, Scotts Valley, CA, USA).

Total intake of SAA from base diet, powder and capsules is 50–60 mg/kg/days SAA and 15–25 mg/kg/days in the SAA_high_ and SAA_low_ group, respectively. In human and animal studies, SAA restriction has usually involved ~ 80% reduction of SAA intake compared to the control group [7]. Notably, data on the normal range of SAA intakes in humans are limited. One paper by Nimni et al*.* estimated that Western and high-protein diets contain up to 50–70 mg/kg body weight/day of SAA in total, in comparison with ~ 20–30 mg/kg body weight/day in vegans/vegetarians [6]. The SAA restricted diet in our planned intervention will meet the WHO recommendations of SAA content of a minimum of 15 mg/kg body weight/day [27].

### Assessment of primary and secondary outcomes

The primary outcome is between-group change in body weight (Table 1). Body weight is measured by the Dual-energy x-ray absorptiometry (DXA) procedure (Lunar iDXA, GE Healthcare Lunar, Buckinghamshire, United Kingdom) giving total body mass in kilograms. The secondary outcome measures include energy expenditure measured in a WRIC to calculate REE [28], body composition by DXA, body anthropometry (WC, hip circumference, height) and a range of metabolites related to SAA metabolism, other amino acids, lipid parameters, appetite hormones and gene expression profiles in adipose tissue to explore additional potential benefits of an SAA restricted diet. Methods and validation for measurements have been published for amino acid profiles [29], sulfur metabolite/aminothiol analyses including hydrogen sulfide (H_2_S) [30], total fatty acid profile [31], appetite hormones and adipokines [32, 33]. Glucose and insulin will be measured as part of the routine clinical laboratory panel for calculation of Homeostatic Model Assessment for Insulin Resistance (HOMA). This panel also includes C-peptide. Liver biomarkers including alanine aminotransferase (ALAT), aspartate aminotransferase (ASAT), lactate dehydrogenase (LD), creatine kinase (CK), alkalic phosphatases (ALP), gamma-glutamyltransferase (ɤ-GT) and the fatty liver index (based on BMI, WC, triglycerides and ɤ-GT) will be assessed to evaluate liver function and hepatic steatosis [34]. Nitrogen balance will be assessed using established methods [35, 36]. Outcome information will be collected at baseline, after 4 and at the final visit.

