## Abstract

**Background:**

Dietary sulfur amino acid (SAA) restriction is an established animal model for increasing lifespan and improving metabolic health. Data from human studies are limited. In the study outlined in this protocol, we will evaluate if dietary SAA restriction can reduce body weight and improve resting energy expenditure (REE) and parameters related to metabolic health.

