### Sample size

Little is known about the effects of a SAA restricted diet on body weight and we have thus based power calculations on data from generic vegan interventions [38]. The online tool GLIMMPSE (https://v2.glimmpse.samplesizeshop.org) was used for power calculations [39]. With two groups and three repeated measures we will test for a significant group by time interaction in the study, indicating differences in body weight over time between the groups. Desired power is 0.8 and alpha was set to 0.05. A body weight difference of 3 kg between groups at the end of the study is considered clinically meaningful. The average body weight at baseline was set to 90 (SD 6) kg. A mean body weight difference of 1 and 3 kg between the SAA_low_ and SAA_high_ after 4 weeks and 8 weeks was set in the power calculations, respectively. Baseline body weight is generally strongly correlated with body weight at subsequent visits. We hypothesize a correlation of 0.9 between repeated measurements of body weight in each subject at each study visit and a decay rate of this correlation coefficient of 0.5 per visit. This yielded a total sample size of 46. Accounting for 25% dropout (46/1 − 0.25), the total sample size is 60 corresponding to 30 participants per group. The design file used for sample size calculations is available in the supplementary material and can be uploaded to GLIMMPSE to view results and design choices (Additional file 3).

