### Statistical analysis

Our study design includes two intervention groups and three repeated measurements (baseline, 4 weeks, final visit). To control for correlated observations per subject per visit, the analysis of outcomes will be by linear mixed model regression. This model will include the treatment covariate, the visit covariate and their interaction term and a random term to control for within-subject correlation. The primary outcome variable is change in body weight. The interaction term will indicate change over time in body weight by intervention group. Depending on the pattern of missing observations and loss to follow-up, missing values will be handled with multiple imputations or model approaches (including linear mixed models which are robust to missing observations), and sensitivity analyses will be performed as recommended [40, 41].

We expect that there will be treatment heterogeneity indicating that effects may differ depending on covariate values at baseline. For example, baseline body weight is highly predictive and correlated to body weight change during an intervention. All models will thus be adjusted for the baseline values of the outcome variable. In addition, the models will be adjusted for the blocking factor used in randomization.

The analyses will be performed according to the intention-to-treat approach, but per-protocol (in which noncompliant participants are excluded) analyses will also be reported as recommended by the CONSORT guidelines [21].

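### Resting energy expenditure is planned without adjustment for body size at the same visit, so the assumed weight loss would attenuate, and may mask, a mass-independent rise

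*Protocol article*

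**What the plan says.** REE appears first among the secondary outcomes in Table 1. Under Assessment of primary and secondary outcomes the protocol states: "The secondary outcome measures include energy expenditure measured in a WRIC to calculate REE". The same section has outcomes, including body composition by DXA, collected at baseline, week 4 and the final visit.

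The hoped-for effects are paired in the Abstract: "we will evaluate if dietary SAA restriction can reduce body weight and improve resting energy expenditure (REE"). The Introduction gives the animal rationale, in which higher expenditure goes with lower adiposity. It also makes the search for mechanisms the second aim of the trial.

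The Statistical analysis section describes one linear mixed model for outcomes, with treatment, visit, their interaction and a random subject term. On covariates it says: "All models will thus be adjusted for the baseline values of the outcome variable". It then adds the blocking factor used in randomisation. It names no other covariate, and nowhere does the article relate REE to weight, lean mass or fat mass measured at the same visit.

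The Sample size section sets the expected weight effect: "A mean body weight difference of 1 and 3 kg between the SAA_low_ and SAA_high_ after 4 weeks and 8 weeks".

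**The concern.** The trial hopes for two effects that work against each other in the REE comparison. If the low-SAA diet raises expenditure per unit of tissue, REE goes up. If it also reduces weight, there is less tissue and REE goes down. Baseline REE and the blocking factor are set before treatment, so neither can account for a change in body size during the eight weeks.

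The between-arm REE difference is then the sum of two parts with opposite signs. The better the diet works on the primary outcome, the smaller that sum becomes for a given metabolic effect. A null result on total REE could mean no metabolic effect, or a metabolic rise offset by a smaller body. With mechanism as a stated aim, that distinction matters. The primary outcome and the sample size are not affected.

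**Working it through.** **1. The plan's own figure, from which the 3 kg comes.** Inputs from the Sample size section: "Desired power is 0.8 and alpha was set to 0.05"; "The average body weight at baseline was set to 90 (SD 6) kg"; weight differences of 0, 1 and 3 kg at the three visits; correlation 0.9 with a decay rate of 0.5. Reading the decay as a linear-exponent structure gives 0.9 for adjacent visits and 0.9^1.5 = 0.854 from baseline to week 8. The multivariate F test of group by visit then has power 0.805 at N = 46, the smallest even N that reaches 0.80. The stated 46 is reproduced. (46/0.75 = 61.3 against the stated 60 is a small rounding matter and plays no part here.) So the weight effect used below is the one that the trial is powered for. No REE effect, REE standard deviation or REE slope is given.

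**2. What the planned REE contrast estimates.** Let m be the mass-independent change in REE in the low-SAA arm relative to the high-SAA arm, d the weight by which the low-SAA arm is lighter, and k the fall in REE per kg lost. Then

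- total REE difference = m − k × d.

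The planned model estimates the whole right-hand side.

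**3. Size of k × d without an outside slope.** If REE scales in proportion to weight:

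- week 4: 1/90 = 1.1%
- week 8: 3/90 = 3.3%

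A rough ceiling in kcal under the same scaling uses the energy supplied, 2500 kcal/day for men and 2200 for women, mean 2350. Taking this as total expenditure (an assumption), 2350/90 = 26 kcal/day per kg, and 3 kg gives about 78 kcal/day. REE is only part of total expenditure, so the REE fall would be smaller, and smaller again if the loss is mostly fat.

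**4. Size with an assumed slope.** The slope is an assumption, shown as a range:

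| k (kcal/day per kg) | week 4 (1 kg) | week 8 (3 kg) |
|---|---|---|
| 10 | 10 | 30 |
| 15 | 15 | 45 |
| 20 | 20 | 60 |

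A true rise m of 30 to 60 kcal/day at week 8 would be cancelled in full within this range. A larger rise would only be reduced. A rise of 75 kcal/day, for example, is cancelled only at k = 25, which lies outside it.

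**5. What this could mean for power (illustration only).** Assume 23 per arm, residual REE SD 100 kcal/day and m = 100 kcal/day. By the normal approximation, power = Φ(effect/(100 × √(2/23)) − 1.96).

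| Quantity tested | Effect (kcal/day) | Power |
|---|---|---|
| mass-independent | 100 | 92% |
| total, k = 10 | 70 | 66% |
| total, k = 15 | 55 | 46% |
| total, k = 20 | 40 | 27% |

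The first row is optimistic in one respect: it uses the same SD and ignores the precision lost because arm and body composition are correlated once weight differs. The direction of the comparison follows from the trial's hypotheses. The percentages rest on assumed values of m, k and SD.

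**The case against.** The strongest reply is that nothing in the plan is wrong. Baseline-adjusted REE compared by randomised arm is a valid intention-to-treat estimate of the diet's total effect. If weight loss lowers REE, that is a real consequence of the diet. The Objectives speak of effects on REE and do not promise a mass-independent estimate. This stands. A reader might infer that the planned analysis is biased, but the documents do not support that: it is off target only if it is read as a statement about metabolic rate at a given body size.

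Second, the article is condensed. Naming two covariates for all models does not forbid further models, and an analysis plan that is not shown may already contain one. This also stands, and is why the point is put as an improvement. But the covariates that the article does state cannot answer the mechanistic question.

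Third, the weight difference may not occur. The planning value comes from generic vegan interventions, whereas here both arms eat the same plant-based base diet. With no weight difference the two estimates should agree closely, provided that lean and fat mass also do not differ.

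Fourth, adjusting for same-visit lean and fat mass conditions on variables that treatment may change, so the adjusted contrast loses the full protection of randomisation. That is true. It is the reason to keep total REE and to give the adjusted result a mechanistic label.

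**Conclusion.** The point holds as a limit on interpretation. The two covariates named for all models leave REE as a total effect. If the low-SAA arm loses more weight, as the sample size assumes, that total effect understates any mass-independent rise and may mask it. At the planned 3 kg the offset is about 3.3% under proportional scaling, or 30 to 60 kcal/day at an assumed 10 to 20 kcal/day per kg. It is zero if the arms do not differ in body size.

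Two stronger readings are not supported. One is that the plan will hide the rise: this would need a small true rise or a steep slope, and the documents give neither figure. The other is that REE is the main mechanism under test. It is listed first among the secondary outcomes, but the Introduction names it alongside insulin sensitivity, adiposity, mitochondrial and lipid effects.

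The point is a cheap improvement. The primary analysis and the sample size stay as they are.

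**What to change.** Keep baseline-adjusted total REE as the planned intention-to-treat analysis. Before unblinding, pre-specify one further model:

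- Outcome: REE at weeks 4 and 8.
- Terms: treatment, visit, their interaction and the random subject term, as already planned.
- Covariates: DXA lean mass and fat mass from the same visit, baseline REE, and sex (the stratification factor). Enter the two masses as separate covariates and do not divide REE by kg, since a ratio assumes strict proportionality.

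Report both results side by side. Label the adjusted one mechanistic and supportive, and say that it conditions on post-randomisation body composition. State that total REE alone will not be used to conclude that metabolic rate is unchanged.

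The cost is one extra model on data already collected at the same visits. The downside is a second REE result that may differ from the first and that needs untestable assumptions for a causal reading. Fixing both roles in advance removes the later choice between them.

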### Assessment of baseline diet

To obtain an estimate of the habitual diet of the participants and the magnitude of change in foods and nutrient composition due to the dietary intervention, they will complete a 279-item validated web-based FFQ at baseline [37].

### Monitoring compliance and feasibility

Compliance will be monitored during the intervention using food diaries four days including the day with the free ad libitum meal prior to each study visit as well as compliance questionnaires. The participants will be asked to note which meals or parts of them they did not consume, and if other food items not in the plan have been consumed. The participants’ subjective rating and evaluation of the diets will be collected with questionnaires including visual analogue scales at each study visit. We will measure plasma and urine SAA to objectively monitor compliance. In addition, participants will be asked to return boxes containing capsules.

### Strategies to maintain compliance

The compliance to the dietary interventions or dietary advice is a considerable source of bias. In previous pilot data, the compliance was shown to be > 80% to dietary interventions, which is likely due to the provision of all intervention foods, and the relatively short intervention period of 7 days [19]. We will continue home delivery of foods in the base diet to increase the incentive to adhere to the plan. This delivery will also include a menu with recipes for each meal and information on daily intakes.

After screening and prior to baseline, each participant will be carefully educated through nutritional counselling with study dietitians or dietitian students in their final year of training. During the intervention, the participants will be offered regular consultations with the study dietitians per telephone for encouragement and continuous evaluation of participant adherence. During these phone calls, participants will receive counseling and advice to facilitate motivation and diet adherence. They will also be allowed to ask any questions relating to the intervention, meals and recipes, and raise any concerns. In general, study personnel will be available to the participants via e-mail regarding the intervention at all times.

To limit the effects on the participants’ social life during a restrictive diet, they will be allowed one ad libitum meal per week, but this meal should precede testing days by no less than three days. The content and amount of the ad libitum meals should be noted in the food diaries. For the final week of the intervention, the participants should adhere fully to the study protocol including the meal plan.

### Sample size

Little is known about the effects of a SAA restricted diet on body weight and we have thus based power calculations on data from generic vegan interventions [38]. The online tool GLIMMPSE (https://v2.glimmpse.samplesizeshop.org) was used for power calculations [39]. With two groups and three repeated measures we will test for a significant group by time interaction in the study, indicating differences in body weight over time between the groups. Desired power is 0.8 and alpha was set to 0.05. A body weight difference of 3 kg between groups at the end of the study is considered clinically meaningful. The average body weight at baseline was set to 90 (SD 6) kg. A mean body weight difference of 1 and 3 kg between the SAA_low_ and SAA_high_ after 4 weeks and 8 weeks was set in the power calculations, respectively. Baseline body weight is generally strongly correlated with body weight at subsequent visits. We hypothesize a correlation of 0.9 between repeated measurements of body weight in each subject at each study visit and a decay rate of this correlation coefficient of 0.5 per visit. This yielded a total sample size of 46. Accounting for 25% dropout (46/1 − 0.25), the total sample size is 60 corresponding to 30 participants per group. The design file used for sample size calculations is available in the supplementary material and can be uploaded to GLIMMPSE to view results and design choices (Additional file 3).

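### The trial is tested and sized on a group-by-time interaction over three visits, while the effect it calls clinically meaningful is the difference at week 8; the week-8 contrast should be named as the primary test

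*Protocol article*

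**What the plan says.** The Sample size section of the protocol article fixes the test: "With two groups and three repeated measures we will test for a significant group by time interaction in the study". It then gives the target effect: "A body weight difference of 3 kg between groups at the end of the study is considered clinically meaningful". The planning inputs are "Desired power is 0.8 and alpha was set to 0.05", "The average body weight at baseline was set to 90 (SD 6) kg", and assumed differences between the arms of 1 kg after 4 weeks and 3 kg after 8 weeks. The correlation between repeated weights is 0.9 with a decay rate of 0.5 per visit. The result is 46 participants, raised to 60 for dropout.

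The Statistical analysis section describes the model: "This model will include the treatment covariate, the visit covariate and their interaction term and a random term to control for within-subject correlation". It reads the treatment effect from one place: "The interaction term will indicate change over time in body weight by intervention group". It also names change in weight as the outcome variable and adjusts every model for the baseline value of the outcome. The outcomes section says "The primary outcome is between-group change in body weight" and attaches no time point.

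**The concern.** The Introduction asks whether 8 weeks of restriction reduces overweight and obesity, and the effect size that matters is attached to the end of the study. The named test is a different quantity. With visit as a three-level factor, a group-by-time interaction has (2−1)×(3−1) = 2 degrees of freedom and asks whether the two mean profiles depart from parallel in any way. It has no direction, and it responds to week 4 as well as week 8.

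Two things follow. A significant primary result would not by itself establish a week-8 difference. And a week-8 effect of the planned size would be detected less often than the same data allow. In addition, the model description leaves open which interaction is meant, and at least one admissible version answers a question the trial does not ask.

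**Working it through.** **Inputs.** All are from the Sample size section: SD 6 kg; differences 0, 1 and 3 kg at weeks 0, 4 and 8 (zero at baseline by randomization); alpha 0.05; correlation 0.9 with decay 0.5. Assumptions of this check: the SD is the same at every visit; the decay is read as a linear exponent autoregressive pattern, so the correlation is 0.9 between adjacent visits and 0.9^1.5 = 0.854 between weeks 0 and 8; the 1-df tests are two-sided; allocation is equal.

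**Step 1: reproduce the stated 46.** Take the two changes, week 4 − week 0 and week 8 − week 0.
- Variances: 2×36×(1−0.9) = 7.20 and 2×36×(1−0.854) = 10.53. Covariance: 36×(1−0.9−0.854+0.9) = 5.26.
- Noncentrality: λ = (N/4)·d′V⁻¹d with d = (1, 3). At N = 46, λ = 10.46.
- Critical value of F with 2 and 43 df: 3.214. Power = 0.805.
- At N = 44 the power is 0.785.

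So 46 is the smallest even total that reaches 80% for a 2-df test.

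**Step 2: the week-8 contrast under the same inputs, N = 46, difference 3 kg.**
- Change from baseline: SD √10.53 = 3.24; SE = 3.24×√(4/46) = 0.957; ratio 3/0.957 = 3.14; power 0.866. For 80% power, N = 40.
- Baseline-adjusted: residual SD = 6×√(1−0.854²) = 3.12; SE = 0.921; ratio 3.26; power 0.889. For 80% power, N = 38.

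Against 0.805, the week-8 contrast gains about 6 points (change) to 8 points (baseline-adjusted).

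**Step 3: a week-4 difference with zero at week 8, 2-df test.** Now d = (w, 0), where w is the week-4 difference.

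| Week-4 difference | Significant at N = 46 | Significant at N = 60 |
|---|---|---|
| 1 kg (the planned week-4 value) | 26% | 33% |
| 2 kg (twice the planned value) | 79% | 90% |

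**Step 4: other readings of the model.**
- Visit as a number (0, 4, 8 weeks, equally spaced): with complete data and a random intercept, each slope per visit interval is (week 8 − week 0)/2. The interaction is then 1 df and essentially the week-8 change contrast.
- Baseline as a covariate, weeks 4 and 8 as outcomes: the interaction is 1 df and tests week 8 minus week 4. The planned value is 3 − 1 = 2 kg; SD = √(2×36×0.1) = 2.68; SE at N = 46 = 0.791; ratio 2.53; power 0.70, and N = 60 completers would be needed for 80%. A benefit of 3 kg at both visits would give an interaction of exactly zero.

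**Step 5: sensitivity to the correlation reading, N = 46.**

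| Correlations (lag 1, lag 2) | 2-df interaction | Week-8 change | Week-8 baseline-adjusted |
|---|---|---|---|
| 0.9, 0.854 | 0.805 | 0.866 | 0.889 |
| 0.9, 0.81 (first-order autoregressive) | 0.704 | 0.767 | 0.807 |
| 0.9, 0.9 (constant) | 0.926 | 0.960 | 0.967 |

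The order is the same in every row.

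**The case against.** The strongest reply is that the protocol never says 2 df, omnibus or joint test, nor that visit is categorical. Reproducing 46 says how the power calculation was probably done; it does not fix the analysis. If visit is numeric, the interaction is already close to the contrast proposed here. This stands, and the 2-df form is therefore put forward as an inference. The inference is not airtight either: a baseline-adjusted week-8 contrast also gives 46 under the first-order autoregressive pattern, although that pattern does not match the stated decay of 0.5. What the reply leaves untouched is that two of the three admissible readings do not test the week-8 difference, and the text does not choose between them.

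A reader might infer that the trial is underpowered. The documents do not support that: it is sized on the test it names and keeps its planned 80%. The 6 to 8 points are a comparison with another test, not a shortfall. A reader might also infer an inflated false-positive rate. When the groups differ at no visit, the 2-df test still rejects in 5% of trials.

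It is fair, too, that the 79% requires a week-4 difference twice the planned one that then vanishes while the diet continues. It is an illustration and belongs beside the 26%. Visit-specific estimates from the same model would reveal such a pattern.

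Finally, choosing a contrast is often left to the analysis plan, and one coefficient of a categorical model is the week-8 difference in change. But this article does not leave the test open: it names the interaction and sizes the trial on it.

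**Conclusion.** The point holds in limited form. The named test and the clinically meaningful effect are different quantities under the categorical reading that reproduces 46, and under the reading with baseline as a covariate. Only the numeric-visit reading brings them close together.

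The cost at 46 completers is about 6 to 8 percentage points of power relative to a week-8 contrast, plus a primary result that, if significant, need not mean the groups differ at 8 weeks. If the covariate reading were applied, power on the planned pattern would be about 0.70, and a constant benefit at weeks 4 and 8 would be missed. These figures rest on the stated SD and differences, equal SD at each visit, and the correlation reading above. With the planned 1 and 3 kg pattern, the 2-df interaction and the week-8 contrast would usually agree, so this is a worthwhile improvement and not a flaw that invalidates the design.

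**What to change.** In the Sample size and Statistical analysis sections, name the baseline-adjusted between-group difference in body weight at week 8, estimated from the planned mixed model, as the single primary test and estimate (1 df, two-sided 5%, with 95% CI). State how visit and baseline enter the model, so that only one reading remains. Keep the week-4 difference and the group-by-time interaction as supportive results. Restate power as about 87–89% for 3 kg with 46 completers under the same inputs.

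The cost is rewording in two sections; no participants, visits or measurements are added. The small downside is that no primary claim could rest on a difference seen at week 4 only.

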**Method/design:**

Men and women (calculated sample size = 60), aged 18–45 years, with body mass index of 27–35 kg/m^2^ will be included in a double-blind 8-week dietary intervention study. The participants will be randomized in a 1:1 manner to a diet with either low or high SAA. Both groups will receive an equal base diet consisting of low-SAA plant-based whole foods and an amino acid supplement free of SAA. Contrasting SAA contents will be achieved using capsules with or without methionine and cysteine (SAA_high_, total diet SAA ~ 50–60 mg/kg body weight/day; SAA_low_, total diet SAA ~ 15–25 mg/kg body weight/day). The primary outcome is body weight change. Data and material collection will also include body composition (dual X-ray absorptiometry), resting energy expenditure (whole-room indirect calorimetry) and samples of blood, urine, feces and adipose tissue at baseline, at 4 weeks and at study completion. Measures will be taken to promote and monitor diet adherence. Data will be analyzed using linear mixed model regression to account for the repeated measures design and within-subject correlation.

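### The 60 randomised does not quite cover 25% dropout from 46 evaluable: the intended formula gives 61.3 (62 with equal arms), and 60 covers about 23%

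*Protocol article*

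**What the plan says.** The Sample size section of the protocol article sets out the calculation in one paragraph. The test is the interaction of group and time: "With two groups and three repeated measures we will test for a significant group by time interaction in the study". The error rates are given as "Desired power is 0.8 and alpha was set to 0.05". The effect is specified at both follow-up visits: "A mean body weight difference of 1 and 3 kg between the SAA_low_ and SAA_high_ after 4 weeks and 8 weeks was set". For the spread, "The average body weight at baseline was set to 90 (SD 6) kg". For the correlation, "We hypothesize a correlation of 0.9 between repeated measurements of body weight in each subject at each study visit", with a decay rate of 0.5 per visit.

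The result before dropout is "This yielded a total sample size of 46". The article then allows for 25% dropout with the expression 46/1 − 0.25, and states that "the total sample size is 60 corresponding to 30 participants per group". The Method/design paragraph of the abstract repeats the final figure as "calculated sample size = 60", without comment on power or dropout.

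The Statistical analysis section plans linear mixed models, multiple imputation or model-based handling of missing values, intention-to-treat analysis, and adjustment of all models for the baseline value of the outcome.

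**The concern.** The step from 46 to 60 can be checked from the numbers in that one paragraph, and it fails. Neither the expression as printed nor the expression as intended gives 60. A sample size is normally rounded up after inflation for dropout. Here it went down, and the article does not say that it was rounded.

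What is at stake is the stated dropout allowance. A reader who takes the section at its word believes that a quarter of the participants can be lost and the required 46 will remain. The allowance may well be tested: the Discussion reports that 25% withdrew from the one comparable human methionine-restriction study because the supplement was unpalatable, and that participants in the trial group's own 7-day pilot studies also found it unpalatable.

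**Working it through.** **Inputs** (protocol article, Sample size unless noted): two-group, three-visit interaction test; alpha 0.05, power 0.80; SD 6 kg; group differences of 1 kg at week 4 and 3 kg at week 8; correlation 0.9 with decay 0.5; 46 evaluable; 25% dropout; 60 randomised. The 1:1 allocation is from the abstract. A baseline difference of 0 kg is assumed because the trial is randomised.

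**Step 1. Reproduce the 46.** The design file (Additional file 3) is not shown, so the correlation structure has to be assumed. Read as 0.9 for adjacent visits and 0.9^1.5 = 0.854 for baseline to week 8:
- variance of change to week 4: 36 × 2 × (1 − 0.9) = 7.20
- variance of change to week 8: 36 × 2 × (1 − 0.854) = 10.53
- covariance of the two changes: 36 × (1 − 0.9 − 0.854 + 0.9) = 5.26

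The squared standardised distance for the change differences (1, 3) is 0.910. The noncentrality is 0.910 × n1·n2/(n1 + n2), referred to an F distribution with 2 and N − 3 degrees of freedom.

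| Evaluable N | Noncentrality | Power |
|---|---|---|
| 44 | 10.01 | 0.785 |
| 45 (22 + 23) | 10.23 | 0.795 |
| 46 | 10.46 | 0.805 |

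So 46 is the smallest even total that reaches 0.80, and the article's figure reproduces.

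**Step 2. Inflate for dropout.**
- As printed: 46/1 − 0.25 = 45.75, clearly not what was meant.
- As intended: 46/(1 − 0.25) = 61.33, rounded up to 62, or 31 per arm.
- The common mistake: 46 × 1.25 = 57.5, or 58. This does not explain 60 either.

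**Step 3. What 60 delivers.**
- Completers at 25% dropout: 60 × 0.75 = 45.
- Largest dropout that leaves 46: (60 − 46)/60 = 14/60 = 23.3%.

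Steps 2 and 3 do not depend on the correlation reading.

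**Step 4. Power with 45 completers.**
- Unadjusted two-degree-of-freedom test, completers only: 0.795 (Step 1).
- Two-degree-of-freedom test of the week-4 and week-8 differences, adjusted for baseline. Residual variances are 36 × (1 − 0.9²) = 6.84 and 36 × (1 − 0.854²) = 9.76, with covariance 36 × (0.9 − 0.9 × 0.854) = 4.74. The squared distance is 0.968, the noncentrality is 0.968 × 22 × 23/45 = 10.89, and the power on 2 and 41 degrees of freedom is about 0.82.

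**The case against.** The best defence is that this is a matter of two participants. The method, dividing by one minus the dropout rate, is right; 60 looks like 61.3 taken to a round, even number; the lost parentheses are typographic; and 25% is itself only a planning figure. All of that stands, and it fixes the size of the point. It does not make the sentence correct, because the section presents 60 as accounting for 25% dropout and does not say that it was rounded.

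A reader might go further and infer that the trial fails to preserve 80% power. The document does not support that. The 79.5% counts only completers and ignores the baseline adjustment. The Statistical analysis section already plans that adjustment, and with it 45 completers give about 82%. It also plans methods that can use incomplete data. In an approximate calculation for the unadjusted test, power rises from 0.795 to 0.802 if 5 of the 15 dropouts attend week 4, and to 0.809 if 10 do. The timing of dropout is not stated, so this is a range.

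A reader might also infer that the abstract promises 80% power after 25% loss. It does not: it gives only the number 60 as calculated.

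**Conclusion.** The statement is wrong as written, and the error is minor. On the article's own figures, 25% dropout from 46 evaluable requires 62 randomised with equal arms. The stated 60 leaves 45 at that rate and tolerates 23.3%. This is plain arithmetic and needs no modelling assumption.

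The effect on power is about half a percentage point below target on the unadjusted, completers-only test, and there is none on a baseline-adjusted two-degree-of-freedom test. Those power figures rest on correlations of 0.9 and 0.854 and on the multivariate form of the interaction test. That combination returns 46. Another reading would not: first-order autoregressive correlations of 0.9 and 0.81 with the same test need 58. No design change follows from this point.

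**What to change.** Restore the parentheses and keep 60. Replace the dropout sentence with one to this effect: inflating 46 for 25% dropout gives 46/(1 − 0.25) = 61.3, or 62 with equal arms; the trial randomises 60, rounded down from 61.3, which leaves the required 46 at up to about 23% dropout.

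Add that at 25% dropout the 45 completers give about 79.5% power on the unadjusted two-degree-of-freedom interaction test, and about 82% on a two-degree-of-freedom test with the planned baseline adjustment. State the correlations assumed (0.9 and 0.854), after checking them against the design file.

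The cost is a sentence or two. Recruitment and analysis do not change, and the stated dropout tolerance becomes slightly less favourable.
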